## Abstract

**Background:**

Traditional methods used for prediction of preterm delivery are subjective and inaccurate. The Electrohysterogram (EHG) and in particular the estimation of the EHG conduction velocity, is a relatively new promising method for detecting imminent preterm delivery. To date the analysis of the conduction velocity has relied on visual inspection of the signals. As a next step towards the introduction of EHG analysis as a clinical tool, we propose an automated method for EHG conduction velocity estimation for both the speed and direction of single spike propagation.

**Methods/Design:**

The study design will be an observational cohort study. 100 pregnant women, gestational age between 23 + 5 and 34 weeks, admitted for threatening preterm labor or preterm prelabor rupture of membranes, will be included. The length of the cervical canal will be measured by transvaginal ultrasound. The EHG will be recorded using 4 electrodes in a fixed configuration. Contractions will be detected by analysis of the EHG and using an estimation of the intra uterine pressure. In the selected contractions, the delays between channels will be estimated by cross-correlation, and subsequently, the average EHG conduction velocity will be derived. Patients will be classified as labor group and non-labor group based on the time between measurement and delivery. The average conduction velocity and cervical length will be compared between the groups. The main study endpoints will be sensitivity, specificity, and area under the ROC curve for delivery within 1,2,4,7, and 14 days from the measurement.

**Discussion:**

In this study, the diagnostic accuracy of EHG conduction velocity analysis will be evaluated for detecting preterm labor. Visual and automatic detection of contractions will be compared. Planar wave propagation will be assumed for the calculation of the CV vector.

**Trial registration:**

Current Controlled Trials ISRCTN07603227.

## Background

### Traditional methods for detecting preterm labor

Preterm labor and subsequent preterm birth occur in about 10% of all pregnant patients in developed countries and are the leading cause of neonatal mortality and morbidity [1-3]. Antenatal treatment with tocolytics and corticosteroids can be used to improve the neonatal outcome of preterm birth [4]. However, traditional methods used for predicting preterm delivery are subjective and cannot accurately predict when labor will occur. Intrauterine pressure measurement is invasive and cannot be used for pregnancy monitoring. External tocography, being noninvasive, is extensively used for pregnancy monitoring, but provides only quantification of the number of contractions per time unit [5]. Transvaginal ultrasonic cervical length (TVU CL) measurement is widely used in patients presenting with preterm contractions, but it has only a moderate sensitivity and specificity, especially for intermediate values for cervical length [6]. A relatively new biochemical marker, fetal fibronectin, is currently being introduced for short term prediction of preterm delivery. Its strength lies in ruling out imminent preterm delivery, but it cannot be used to predict when labor will occur [7]. Cervical dilatation is a late sign of imminent delivery and the change of successfully delaying delivery using tocolytics is inversely related to the cervical dilatation [8]. Overall more than 50% of the patients admitted for threatening preterm labor, deliver at term [9-11].

### The electrohysterogram and preterm labor

Labor and delivery are preceded by two physiological phenomena: increased excitability and increased connectivity among the myometrial cells resulting in increased propagation of the action potentials that underlie uterine contractions [12-14]. These changes are reflected in the electrohysterogram (EHG), which is a noninvasive abdominal measurement of the uterine electrical activity. As a relatively new diagnostic tool, the EHG has been shown to have potential for monitoring contractions during labor [15-19], as well as detecting pathological contractions leading to preterm delivery [5,20-28]. Various ways of characterizing the EHG have been proposed, including the spectral content using either the peak frequency [5,22-24] or median frequency [28,29] of the power density spectrum, or the ratio between a high and low frequency band [30]. Alternatively, the non-linear correlation among signals in multichannel EHG recordings has been proposed to predict (preterm) delivery [31,32]. The propagation speed of the electrical activity, referred to as conduction velocity (CV), has been quantified by analyzing either the propagation of whole bursts of uterine electrical activity [33,34], or single spikes within a burst [5,21,35,36] Different physiological phenomena could possibly underlie changes in these types of propagation [37,38]. Recently, the estimated CV based on single spike propagation, has been suggested to be a discriminative parameter of imminent preterm delivery [5].

## Methods and design

### Study population

The population will consist of patients admitted to the obstetrical ward of the Máxima Medical Center Veldhoven and the Jeroen Bosch hospital for threatening preterm labor or preterm prelabor rupture of membranes and who are eligible for treatment with tocolytics and corticosteroids. The decision on treatment will be based on the standard diagnostic tests and local protocol. Administration of tocolytics will be registered: type and dosage, time of administration.

### Ethics

The study has been approved by the research ethics committee of the Máxima Medical Center and is registered under ISRCTN07603227 in the current controlled trial register.

#### Inclusion criteria

• Gestational age between 23 + 5 and 34 + 0 weeks.

• Clinically evaluated symptoms of preterm labor: at least 6 contractions in 60 minutes based on the external tocogram and/or maternal perception.

• Both singleton and multiple gestations will be included.

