### Sample size

During the year 2010, a total of 150 patients were admitted to the obstetrical ward of the Máxima Medical Center for threatening preterm labor which met the inclusion criteria. Approximately 40% of these patients delivered within 7 days. A sample size can be calculated based on an observed difference in test characteristics between the standard diagnostics and the EHG analysis using a fixed allocation ratio of 40 – 60% for the positive and negative group respectively. In the study by Lucovnik et al. an area under the curve of the receiver operating characteristics (ROC) of 0,96 was observed for the EHG analysis and 0,72 for the Bishop score (the best performing test among the standard diagnostics) [5].

A sample of 7 from the positive group and 11 from the negative group achieve 82% power, assuming an area under the ROC curve of 0,95 for EHG CV analysis and 0,70 for the standard diagnostics and using a two-sided *z*-test at a significance level of 0.05. This means a minimal number of 20 patients will need to be included. However, this observed difference is based on a single study. In order to increase the likelihood of detecting a difference in case of a lower observed difference or different allocation ratio, we propose to include a total of 100 patients.

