## Discussion

The study aims to evaluate CV analysis of the EHG as clinical tool for the diagnosis of imminent preterm delivery. In an observational cohort study the EHG will be recorded in patients admitted for threatened preterm labor. The CV will be estimated in the EHG using a fully automated analysis. This automated approach entails a novel automatic selection of contractions based on the eIUP and automatic delay estimation. The diagnostic accuracy will be expressed in terms of sensitivity, specificity and area under the ROC curve for delivery within 1,2,7, and 14 days from the measurement.

Similar to [5], part of the patients will already be treated with tocolytics at the time of the measurement. This could influence the amount of contractions and possibly the CV as well. Using logistic regression, the administration of tocolytics will be tested as possible confounding factor. The EHG CV analysis will be evaluated as diagnostic tool for predicting imminent spontaneous preterm delivery. Although it is not a common scenario in patients admitted for threatened preterm labor, patients within the labor group in which labor is induced will not be included in the final analysis.

Perhaps the biggest challenge and also an essential step in accurate estimation of the CV is recognizing contractions amongst noise and artifacts in the EHG. Different from term patients in labor, preterm patients admitted for threatened preterm labor have mostly an irregular pattern of uterine contractions of a varying frequency as well as duration. Therefore, the detection algorithm cannot assume a regular pattern and fixed duration. Furthermore an external tocodynamometer can fail to show contractions in some patients [40,41]. Therefore, for use as independent clinical tool, the EHG CV analysis cannot rely on the external tocodynamometer as reference. Hence the analysis will be mainly based on the electrical signal recorded on the skin.

Our methods will entail filtering in a narrow frequency band (0,3 – 0,8 Hz) in order to suppress signals other than uterine activity, including (abdominal) striated muscle activity and the maternal electrocardiogram. The eIUP will be used in order to distinguish uterine activity from the background noise. Visual review of the data is envisaged to evaluate the performance of the automatic algorithm.

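### Eligibility of non-contracting women with ruptured membranes is unclear, and cervical length is measured only with intact membranes, so the EHG and cervical-length accuracy figures come from different women

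*Protocol article*

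**What the plan says.** All references are to the protocol article.

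- **Abstract, Methods/Design:** women "admitted for threatening preterm labor or preterm prelabor rupture of membranes, will be included".
- **Study population:** women admitted "for threatening preterm labor or preterm prelabor rupture of membranes and who are eligible for treatment with tocolytics and corticosteroids", at two hospitals.
- **Inclusion criteria:** "Clinically evaluated symptoms of preterm labor: at least 6 contractions in 60 minutes based on the external tocogram and/or maternal perception". The list has no separate entry or exception for ruptured membranes.
- **Inclusion and measurement:** cervical length by transvaginal ultrasound is done as a standard test when membranes are intact. The EHG is recorded without any such condition.
- **Study parameters/Endpoints:** sensitivity, specificity and AUC are planned for the EHG parameters and for cervical length, at the same delivery cutoffs.
- **Sample size:** the planning data are 150 women "admitted to the obstetrical ward of the Máxima Medical Center for threatening preterm labor which met the inclusion criteria", and "Approximately 40% of these patients delivered within 7 days". The size is derived from a difference in AUC between EHG and standard diagnostics.
- **Discussion:** "In an observational cohort study the EHG will be recorded in patients admitted for threatened preterm labor".

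**The concern.** There are two linked issues.

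**Eligibility.** The abstract and the Study population section name ruptured membranes as a reason for admission alongside threatened labor. The inclusion list sets a contraction frequency and is silent on membranes. The Sample size section and the Discussion name threatened labor only. A reader cannot tell whether a woman with ruptured membranes who contracts less often than the criterion may be enrolled. This matters for the index test, because conduction velocity is calculated only in segments selected as contractions. A woman with none would have no value.

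**Comparison.** Membrane status decides who receives the comparator test. If the plan is followed as written, EHG accuracy is estimated in all women and cervical-length accuracy only in those with intact membranes. A difference between the two AUCs could then reflect the tests, the women, or both. The pooled EHG AUC also averages over two clinical presentations without showing whether the test performs alike in each.

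**Working it through.** **1. Eligibility, section by section**

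| Section | Ruptured membranes named? | Contraction frequency required? |
|---|---|---|
| Abstract, Methods/Design | yes | not stated |
| Study population | yes, with eligibility for tocolytics and corticosteroids | not stated |
| Inclusion criteria | no | yes, no exception |
| Sample size | no | through the reference to the inclusion criteria |
| Discussion | no | not stated |

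On one reading, the inclusion list is a further condition on everyone admitted for either reason. On the other, ruptured membranes is a route of entry of its own. No sentence chooses between them. On either reading some women with ruptured membranes can enter, and the condition attached to the cervical-length measurement shows that they are expected.

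**2. Which women contribute to which figure**

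| Membranes | EHG | Cervical length |
|---|---|---|
| Intact | yes | yes |
| Ruptured | yes | not planned |

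The pooled EHG AUC uses both rows and the cervical-length AUC uses the first row only. This follows from the measurement plan and holds on either eligibility reading.

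**3. The plan's own power figure**

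Inputs from the Sample size section: 7 positive and 11 negative women, AUC 0.95 against 0.70, two-sided z-test, alpha 0.05, stated power 82%.

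Power = Φ((|A1 − A2| − 1.96 × SE_null) / SE_alt), for one curve against a fixed value, with the null at 0.95 and the alternative at 0.70.

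- Hanley-McNeil variance: (0.25 − 1.96 × 0.0616) / 0.1332 = 0.97, power 83.4%.
- Obuchowski variance: (0.25 − 1.96 × 0.0642) / 0.1319 = 0.94, power 82.7%.

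The stated 82% is reproduced to within 2 points by this set-up. Two independent curves with the same numbers give 40%. Two correlated curves reach 82% only at a correlation of about 0.8.

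**4. Size of the like-for-like comparison**

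Assumptions, because the protocol gives no figures: 10% to 40% of the 100 women have ruptured membranes; 40% of those with intact membranes are positive (the planning rate); the correlation between the two AUC estimates is r = 0.3; 0.70 stands in for cervical length, although the plan takes its comparator value from the Bishop score in a cited study. The 0.85 is a less optimistic EHG value chosen for illustration.

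SE_diff = √(SE1² + SE2² − 2r × SE1 × SE2), with Hanley-McNeil SEs; power = Φ(|A1 − A2| / SE_diff − 1.96).

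Example with 60 women (24 positive, 36 negative), 0.85 against 0.70: SEs are 0.0544 and 0.0710. SE_diff = √(0.00296 + 0.00504 − 0.00232) = 0.0754. Then 0.15 / 0.0754 − 1.96 = 0.03, power 51%.

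| Women with intact membranes | Positive / negative | Power, 0.95 v 0.70 | Power, 0.85 v 0.70 |
|---|---|---|---|
| 100 | 40 / 60 | 99.7% | 73% |
| 90 | 36 / 54 | 99% | 69% |
| 80 | 32 / 48 | 99% | 63% |
| 70 | 28 / 42 | 98% | 58% |
| 60 | 24 / 36 | 95% | 51% |

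The correlation matters: at 60 women and 0.85 against 0.70, power is 39% for r = 0 and 73% for r = 0.6.

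**5. Does the 40% planning rate matter?**

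At 100 women and 0.95 against 0.70, power is 99% or more for rates from 30% to 60% (r = 0.3). At 0.85 against 0.70 it is 65%, 73%, 78% and 79% at 30%, 40%, 50% and 60%. With the formula that reproduces the plan's figure, the minimum number for 82% power runs only from 21 to 16 over that range.

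**The case against.** The strongest reply is that the eligibility sections do not conflict. Study population gives the reason for admission and Inclusion criteria adds conditions, so both apply and the population is defined. The Study population section also requires eligibility for tocolytics and corticosteroids, so ruptured membranes alone never suffice. The Discussion wording may be shorthand. A woman below the contraction threshold may still contract and yield a conduction velocity. All of this stands, and it reduces the eligibility issue to an ambiguity.

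A reader might infer that the two hospitals will enrol different populations. The text shows only that they could read it differently.

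A reader might also infer that the 40% rate belongs to another population and undermines the sample size. The documents do not support this. A planning rate does not determine whom sites enrol. The 150 women are described as having met the inclusion criteria, the protocol chose 100 partly to allow for a different split between groups, and step 5 shows little effect at the planned AUCs. Any recalculated rate would rest on assumed inputs.

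Finally, subgroup accuracy is commonly left to an analysis plan, and a regression on background variables that differ between groups is already planned. That answers a bare request for a subgroup table. It does not answer the comparison: the article itself sets the accuracy of two tests side by side while restricting one of them by membrane status. A regression adjustment does not supply cervical-length values that were never measured.

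**Conclusion.** The point holds in two parts of unequal weight.

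First, it is unclear whether a woman with ruptured membranes and fewer contractions than the inclusion list requires is eligible. The abstract, Study population, Inclusion criteria, Sample size and Discussion sections must be reconciled. The document does not settle which reading is intended.

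Second, and more important for the results, the planned EHG and cervical-length AUCs come from different women, and the pooled EHG figure mixes membrane groups. This follows from the text without assumptions. The size of any resulting distortion cannot be given, because the protocol has no figure for the share with ruptured membranes or for test performance in them.

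Restricting the comparison to intact membranes leaves 90 to 60 women under the assumed shares. At the planned AUCs that is ample (99% to 95% power); at 0.85 against 0.70 it is modest (69% to 51%), resting on r = 0.3 and 40% positives.

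**What to change.** 1. State once whether the contraction criterion applies to women admitted with ruptured membranes, and make the five sections named above agree. The choice belongs to the investigators.
2. Report EHG AUC, sensitivity and specificity separately for intact and ruptured membranes, next to the pooled figure.
3. Base the EHG versus cervical-length comparison on women with intact membranes, where both tests are available, and give the number contributing.

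The cost is a wording change and one extra table from data the study collects anyway. The downside is that fewer than 100 women contribute to the comparison, so its precision is lower, and the EHG estimates within each membrane group will be less precise than the pooled one. No recount of the 2010 admissions and no change to the planned 100 women follows from this point.

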#### Exclusion criteria

• Patients in active labor: cervical dilatation >3 cm.

• Signs of infection: baseline fetal heart rate >160 and/or maternal temperature ≥38,0.

• Signs of fetal distress: the following cardiotocogram (CTG) characteristics [39].

○ Baseline heart frequency <100 or >170

○ Reduced variability: <5 bpm during >60 min

○ Complicated variable decelerations, duration >60 sec

Repeated late uniform decelerations.

### Inclusion and measurement

After written informed consent is acquired, patients will be enrolled in the study. In accordance with local protocol, a CTG registration of at least 30 minutes will be performed and maternal temperature will be measured for all patients. In case of intact membranes a TVU CL measurement will be performed as standard diagnostic test. The length of the cervical canal will be measured in a straight line, the shortest of three measurements will be recorded. Simultaneous with the CTG, the EHG will be recorded using a patch containing 4 monopolar electrodes in a diamond shaped pattern and a ground electrode (Nemo Healthcare B.V.). This patch is placed on the middle of the abdomen, just below the umbilicus. A reference electrode is placed on the left anterior superior iliac spine, see Figure 1. Minimal recording length is 30 minutes. The signals will be amplified and stored on the Porti amplifier (Twente Medical Systems International B.V.). The Porti amplifier will be used in a configuration that does not provide any visible reading of the measurement and the data will be stored directly on its flash memory. All diagnostic tests will be performed within 24 hours after admission.

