### Study parameters/Endpoints

Patients will be classified as labor group and non-labor group based on the interval between measurement and delivery. The cutoff points will be delivery within 1, 2, 7, and 14 days of the measurement. As primary outcome the EHG parameters will be compared between these groups in terms of amplitude and angle of the CV. In order to be independent of the number of analyzed segments and contractions per patient, the average CV vector will be identified for each analyzed contraction and subsequently the average CV vector for each patient will be determined. As secondary analysis the TVU CL will be compared between the labor and non-labor group. The sensitivity and specificity will be calculated for the EHG parameters and TVU CL for predicting preterm delivery within 1, 2, 7, and 14 days. In order to be independent on arbitrarily chosen cutoff points, the area under the curve of the receiver operating characteristics will be determined.

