### Statistical analysis

Baseline characteristics will be determined for the labor and non-labor group. Differences will be tested for statistical significance using a fisher exact test for dichotomized variables and a non-paired *t*-test for continuous variables. We will evaluate the influence of significant differences in background variables on the outcome using a multivariate logistical regression model.

The Shapiro–Wilk test will be applied to test for a normal distribution of the estimated values of the CV vector amplitude. Levene’s test will be applied to test for equal variances in the labor and non-labor group. An independent samples t-test will be used to test for a significant difference in amplitude of the CV between both groups. The alpha will be set to 0.05 for all statistical tests. Using contingency tables, the sensitivity and specificity of the EHG and standard diagnostics will be determined.

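### EHG accuracy is computed in all women and cervical-length accuracy only in women with intact membranes, and the AUC difference that sized the study has no planned test

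*Protocol article*

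**What the plan says.** All references are to the Protocol article.

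- **Who is enrolled.** Study population admits women with "threatening preterm labor or preterm prelabor rupture of membranes and who are eligible for treatment with tocolytics and corticosteroids". The Abstract agrees.
- **Who gets which test.** Under Inclusion and measurement, the EHG carries no condition on membrane status: "Simultaneous with the CTG, the EHG will be recorded using a patch containing 4 monopolar electrodes". Cervical length does: "In case of intact membranes a TVU CL measurement will be performed as standard diagnostic test".
- **What is reported.** Study parameters/Endpoints plans: "The sensitivity and specificity will be calculated for the EHG parameters and TVU CL for predicting preterm delivery within 1, 2, 7, and 14 days". The AUC is to be determined as well. No common analysis set is named.
- **What sized the study.** Sample size: "A sample size can be calculated based on an observed difference in test characteristics between the standard diagnostics and the EHG analysis". The calculation is a two-sided z-test at 0.05 of AUC 0.95 (EHG) against 0.70 (standard diagnostics). It gives 82% power with 7 positive and 11 negative women. The total is then raised to 100 to allow for a smaller difference or another allocation ratio.
- **What is analysed.** Statistical analysis gives a t-test of conduction velocity (CV) amplitude between the labor and non-labor groups, and: "Using contingency tables, the sensitivity and specificity of the EHG and standard diagnostics will be determined". It names no test of one AUC against the other.

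**The concern.** There are two linked problems.

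First, cervical length is missing by design, and membrane status decides for whom. Rupture may relate both to the time to delivery and to CV. An EHG AUC from all women set beside a cervical-length AUC from the intact subset can therefore differ because of case mix, even if the two tests perform alike in the women who have both.

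Second, the study is sized on one hypothesis (a difference between two AUCs) and analysed on another (a difference in mean CV between outcome groups). This is more than detail left to an analysis plan, because the article states both the sizing test and the analysis, and they do not match. If cervical length is the comparator, the women who can inform the sizing contrast are those with both tests, not all 100.

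**Working it through.** **1. The plan's own figure.** Inputs from Sample size: AUCs 0.95 and 0.70, 7 positive and 11 negative, two-sided 0.05. With the binormal variance at equal SDs, Var(A) = exp(−a²/2)·(a²+8)·(1/n₁+1/n₀)/(32π), where a = √2·Φ⁻¹(A):

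- A = 0.95: a² = 5.41, Var = 0.00208
- A = 0.70: a² = 0.55, Var = 0.0151
- Null SE, both AUCs at 0.95, correlation 0: √(2 × 0.00208) = 0.0646
- Alternative SE: √(0.00208 + 0.0151) = 0.131
- Power = Φ[(0.25 − 1.96 × 0.0646)/0.131] = Φ(0.94) ≈ 82.7%

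So the stated 82% can be reproduced, with zero correlation, that is, as if the tests were unpaired. The document states neither the correlation nor the null variance. Other variants at correlation 0 give about 40–70%.

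**2. Women with both tests.** The 40/60 split at 7 days and N = 100 are from the document. The rupture share, and 60% of ruptured women delivering within 7 days, are assumptions.

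- 20% ruptured: 12 deliver, 8 do not; 28/52 remain
- 30% ruptured: 18 and 12; 22/48 remain
- 40% ruptured: 24 and 16; 16/44 remain

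**3. Power of a paired AUC test.** Hanley–McNeil variance: [A(1−A) + (n₁−1)(Q₁−A²) + (n₀−1)(Q₂−A²)]/(n₁n₀), with Q₁ = A/(2−A) and Q₂ = 2A²/(1+A). The correlation r = 0.3 between the two AUC estimates is assumed. Power = Φ(difference/SE − 1.96).

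Example at 22/48: the SEs are 0.0335 (0.95), 0.0553 (0.85) and 0.0708 (0.70).

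- 0.95 v 0.70: SE of difference = √(0.0335² + 0.0708² − 0.6 × 0.0335 × 0.0708) = 0.0686; Φ(3.64 − 1.96) = 95%
- 0.85 v 0.70: SE of difference = 0.0756; Φ(1.98 − 1.96) = 51%

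| Positive/negative | 0.95 v 0.70 | 0.85 v 0.70 |
|---|---|---|
| 40/60 (all 100) | 99.7% | 73% |
| 28/52 | 98% | 60% |
| 22/48 | 95% | 51% |
| 16/44 | 89% | 41% |

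At r = 0 the 0.95 v 0.70 column reads 98.6%, 94%, 89% and 79%. At r = 0.3, the smallest EHG AUC with 80% power against 0.70 is about 0.86 at 40/60, 0.90 at 22/48 and 0.93 at 16/44.

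**4. Case mix.** Assumptions: 30% ruptured, 65% of them delivering within 7 days (not the 60% of step 2), 40% overall, EHG AUC 0.755 within each membrane group, and rupture shifting CV by s SD. Per 100 women: positives 19.5 ruptured and 20.5 intact; negatives 10.5 ruptured and 49.5 intact. The separation is d = √2·Φ⁻¹(0.755) = 0.976. Of the 40 × 60 = 2,400 positive–negative pairs:

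- same membrane status: (19.5 × 10.5 + 20.5 × 49.5)/2,400 = 0.508, AUC 0.755
- ruptured positive with intact negative: 965.25/2,400 = 0.402, AUC Φ((d+s)/√2)
- intact positive with ruptured negative: 215.25/2,400 = 0.090, AUC Φ((d−s)/√2)

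For s = +0.5: 0.508 × 0.755 + 0.402 × 0.852 + 0.090 × 0.632 = 0.78. For s = −0.5 the last two AUCs swap, giving 0.71. At ±1 SD the range is 0.66 to 0.80. With only 10% ruptured, ±0.5 SD gives 0.74 to 0.76.

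Case mix can also act through discrimination. Suppose both tests have AUC 0.70 in intact women, 30% are ruptured and 60–70% of those deliver within 7 days. By simulation, the all-women EHG AUC is about 0.62–0.64 if EHG separates poorly in ruptured women (0.2 SD) and about 0.75 if it separates better there (1.2 SD).

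**The case against.** A reader might infer that the protocol makes a head-to-head superiority claim on different patients. It does not. The primary outcome compares CV amplitude and angle between labor and non-labor women. The secondary analysis compares cervical length between the same outcome groups. The Discussion states the aim as evaluating the accuracy of EHG. The contrast between tests is implied by Sample size and by the parallel accuracy measures, not written as a hypothesis. Nor are the patients different: women with cervical length are a subset of those with EHG.

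A reader might also infer that 100 is too few. For the protocol's own 0.95 v 0.70 the table does not support that. The loss concerns smaller differences, although Sample size gives a smaller difference as one reason for 100. The 0.85 is a sensitivity case chosen here, and it has only 73% power even with all 100 women.

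Three further points stand in part.

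- The sizing comparator is called standard diagnostics, and the AUC of 0.72 cited in support belongs to a Bishop score. Inclusion and measurement does call cervical length a standard diagnostic test, so that reading is reasonable but not fixed by the text.
- The inclusion criterion of at least 6 contractions in 60 minutes may lower the rupture share, but does not remove these women.
- Regression on baseline variables that differ could include membrane status, but would not put the two AUCs on the same women.

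The variance method could be left to a document not shown. That does not explain an analysis section that omits the test used for sizing.

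**Conclusion.** The point holds in a limited form. Followed as written, the plan sets an all-women EHG AUC beside an intact-only cervical-length AUC and never tests the difference on which it was sized. Both facts come from the text.

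The size does not. The rupture share, the delivery rate after rupture, the CV shift and the AUC correlation are all assumed. Under those assumptions an overall EHG AUC can move from 0.755 to anywhere between about 0.71 and 0.78 through case mix alone. That is at most about 0.03 in favour of EHG and 0.04 against it at ±0.5 SD. Power at r = 0.3 stays about 89–98% for the stated contrast and falls to 41–60% for 0.85 v 0.70.

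Severity is should-fix: both tests are recorded in women with intact membranes, so the needed analysis remains possible without changing enrolment or measurement.

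**What to change.** Add to Statistical analysis: the AUCs of EHG CV amplitude and TVU CL for delivery within 7 days are compared by a paired method (for example DeLong) in women with intact membranes who have both tests, with a 95% CI of the difference. Seven days is proposed because the 40/60 split in Sample size refers to it; the other horizons can stay descriptive.

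Report EHG sensitivity, specificity and AUC separately for intact and ruptured membranes.

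In Sample size, name the comparator, the assumed correlation and the expected number of women with both tests, and give the detectable AUC difference for that number instead of for 100.

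The cost is wording and a few lines of code, with no extra patients or procedures. The downside is that the stated precision of the comparison becomes less favourable.
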